### Primary and secondary outcomes

The primary outcome will be patient survival at ICU discharge. Patient outcomes will also be recorded at hospital discharge. Additional outcomes include ICU and hospital length of stay, renal function recovery during hospitalization (defined above), and adverse events related to CRRT (defined above).

### Sample size

Due to the observational nature of CRRTnet, a formal sample size calculation was not performed. However, our target recruitment is 2000 patients, which would result in the largest and most detailed collection of CRRT patients to date.

### Statistical analysis

All descriptive data will be analyzed using standard statistical methods. CRRTnet will assess for potential associations between patient characteristics, CRRT initiation and prescription parameters, and patient outcomes (mortality, length of stay, duration of AKI) using ANOVA (for normally distributed variables) or Kruskal-Wallis (for non-normally distributed variables). Multivariate proportional hazards models will be constructed, with initial inclusion of variables with <0.2 significance in univariate analyses. Additional analyses of registry data will be developed based on specific research questions.

Data analyses will be performed by Technomics Research, LLC (Minneapolis, MN) and guided by the CRRTnet registry board.

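### The primary outcome is yes/no survival at ICU discharge, but no stated adjusted analysis estimates it: proportional hazards is the only multivariable model named, and mortality is placed under ANOVA or Kruskal-Wallis

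*Protocol article*

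**What the plan says.** Under Primary and secondary outcomes, the protocol article states: "The primary outcome will be patient survival at ICU discharge". It adds: "Patient outcomes will also be recorded at hospital discharge". Both are statuses read at a time that differs from patient to patient, with no fixed horizon.

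Under Statistical analysis, associations are to be assessed between patient characteristics, CRRT parameters and "patient outcomes (mortality, length of stay, duration of AKI) using ANOVA (for normally distributed variables) or Kruskal-Wallis (for non-normally distributed variables". The adjusted analysis is then given in one sentence: "Multivariate proportional hazards models will be constructed, with initial inclusion of variables with <0.2 significance in univariate analyses". That sentence names no event, time origin or censoring rule, and does not say which outcome the model is for. The section names no chi-square test, logistic regression or other binary-outcome method. It ends by leaving further work open: "Additional analyses of registry data will be developed based on specific research questions".

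**The concern.** The registry exists to compare CRRT practices by patient outcome, and such comparisons need adjustment. The Discussion, for example, plans to relate fluid removal rates to mortality and renal recovery, and its hypothesis is stated after adjustment for severity of illness. The adjusted estimate will therefore carry the conclusions.

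For the primary outcome that estimate should concern the chance of leaving ICU alive, which depends on two rates: how fast patients die and how fast they are discharged alive. A hazard ratio for death with live discharge censored describes only the first. A practice that slows live discharge, or slows both events equally, can then look neutral or protective when ICU survival is worse or unchanged.

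Two smaller problems sit in the same sentence.
- Death cuts length of stay and duration of AKI short, so a practice that kills early can appear to shorten them.
- Duration of AKI is not among the outcomes in the outcomes section and has no operational definition. No AKI onset date appears in the data tables.

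**Working it through.** There is no power or precision figure to reproduce. The Sample size section says "a formal sample size calculation was not performed", and 2000 is only a recruitment target. The check is of the methods.

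**1. Univariate tests on a 0/1 outcome.** One data set was simulated with N = 2000 in three groups (700, 700, 600) and true event rates of 50%, 45% and 55%.
- Pearson chi-square = 9.795, p = 0.00746.
- Kruskal-Wallis H = 9.790, p = 0.00748. This is (N − 1)/N times chi-square: 1999/2000 × 9.795 = 9.790.
- ANOVA p = 0.00743.

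Type I error at nominal 5% was then estimated from 3000 replicates per setting, with event rates of 50% or 5% and groups of 700/700/600 or 1800/100/100. It lay between 4.5% and 5.6% for both tests. The p-values are therefore nearly right. What is missing is an effect measure such as a risk difference or odds ratio.

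**2. Adjusted model.** The article gives no daily hazards and no expected ICU mortality. The Background section says only that hospital mortality approaches or exceeds 50%. Assume constant daily hazards d (death in ICU) and a (live discharge). Then:
- ICU mortality = d/(d + a).
- Odds of ICU death = d/a.
- Hazard ratio for death, with live discharge censored = d(exposed)/d(reference).

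So the odds ratio for ICU death is the death hazard ratio divided by the live-discharge hazard ratio.

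| Setting | d | a | Death HR | ICU mortality | OR for ICU death |
|---|---|---|---|---|---|
| Reference | 0.04 | 0.05 | – | 0.04/0.09 = 44% | – |
| Both halved | 0.02 | 0.025 | 0.50 | 0.02/0.045 = 44% | 0.8/0.8 = 1.0 |
| Live discharge halved | 0.04 | 0.025 | 1.00 | 0.04/0.065 = 62% | 1.6/0.8 = 2.0 |

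A separate simulation of 200,000 patients, with 0.05 per day for each event in the reference group (50% mortality), agrees:
- Discharge hazard halved: HR 1.00, mortality 50% against 67%, OR 2.0.
- Both halved: HR 0.51, mortality 50% against 50%, OR 1.0.
- Death hazard × 0.75 and discharge hazard × 0.5: HR 0.75, mortality 50% against 60%, OR 1.5. Here the direction reverses.

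**3. Length of stay.** Under the same constant hazards, mean stay is 1/(d + a). In the reference it is 1/0.09 = 11.1 days. Doubling the death hazard to 0.08 gives 1/0.13 = 7.7 days, while mortality becomes 0.08/0.13 = 62%. The shorter stay comes entirely from more deaths.

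**4. Duration of AKI.** The outcomes section lists survival, lengths of stay, renal recovery and adverse events. The operational definitions cover recovery categories but not AKI duration. Table 1 has the ICU admission date, the time to CRRT initiation and two creatinine values. Neither it nor Tables 2 and 3 lists an onset date.

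**The case against.** **The univariate tests may be used properly.** The section speaks of associations, so it can be read as comparing continuous characteristics between survivors and non-survivors, where ANOVA and Kruskal-Wallis are correct. Even on a yes/no outcome they nearly reproduce chi-square. This stands: a reader might infer that the mortality p-values would be wrong, and the check shows they would not be materially so.

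**The plan does not say it censors live discharge.** This also stands. A reader might infer that the plan mishandles death and discharge as competing events, but the section gives no censoring rule, and an article may leave that to a fuller document. Cause-specific and subdistribution models are both proportional hazards models, and a cause-specific hazard is a legitimate quantity if labelled as such. Nor does observation end at ICU discharge, since outcomes are also recorded at hospital discharge. For the same reason, the gap between a Kaplan-Meier estimate and cumulative incidence is not evidence against this plan, because the article names no Kaplan-Meier analysis.

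**Length of stay might be analysed in survivors.** The article does not say either way, and excluding CRRT of under 24 h removes the earliest deaths. Later deaths remain, so the handling still has to be stated.

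**This is a registry with open-ended further analyses.** That is true, but the sentence leaving them open refers to specific later research questions. It does not supply an adjusted analysis of the primary outcome.

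**Conclusion.** The point holds in a limited form. The article states a binary primary outcome and names methods for mortality, and none of the adjusted methods named estimates that outcome. This is a mismatch between two stated sections, not merely detail left to an analysis plan.

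The univariate part is loose wording with little consequence for p-values. The adjusted part can change a conclusion. If live discharge is censored, the death hazard ratio can be 0.50 with ICU mortality unchanged at 44%, or 1.00 while mortality rises from 44% to 62%. It can also point the opposite way to the odds ratio (0.75 against 1.5).

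These figures rest on assumed constant hazards and chosen effects. They show what is possible. A reader might take them as the bias to expect in this registry, but the article gives neither ICU mortality nor daily hazards, so they cannot bear that meaning. The points on length of stay and duration of AKI are secondary.

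**What to change.** - **Primary outcome.** Name multivariable logistic (or risk) regression accounting for centre as the adjusted analysis of survival at ICU discharge, and the same for hospital survival. Use chi-square for categorical factors, and report effect estimates with intervals.
- **Proportional hazards, if kept.** State the event and the time origin, allowing for the exclusion of patients with under 24 h of CRRT (for example, a clock starting at 24 h). Treat live discharge as a competing event, either with cause-specific hazards for both events or with cumulative incidence.
- **Length of stay.** Report it separately in survivors and non-survivors, or with death as a competing event.
- **Duration of AKI.** Define it from data that are collected, or drop it.

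The cost is a change of analysis wording and code, and slightly more complex reporting. The primary-outcome change needs no new data, because status at ICU and hospital discharge is already recorded. That does not extend to every alternative. Day-28 measures or days free of renal replacement therapy may need more than is listed: outcomes run to hospital discharge, CRRT prescription details stop at day 14, and only the first course counts.

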### Data collection

Data will be collected encompassing a wide range of variables examining patient characteristics at enrollment, describing daily ICU course, capturing details of CRRT, and describing patient outcomes. Each participating medical center utilizes an electronic medical record which will serve as the primary source for data extraction.

The initial intake form includes demographic variables, and baseline patient characteristics at the time of CRRT initiation (Table 1). Fluid balance (in liters) between the time of ICU admission and CRRT initiation will be collected and used to calculate percent fluid overload using the following formula: [16, 17].

**Table 1 Tab1:** Planned data collection at time of enrollment (CRRT initiation)

Category	Data Elements
Demographics	Date of birth/Age
	Gender
	Body mass index
	Hospital admission weight
Comorbidities	Components of Charlson Index
ICU Admission Data	ICU admission date
	Admission source (hospital ward, emergency department, outside hospital transfer)
	Primary condition
	Secondary condition
CRRT Initiation Data	Clinical indication for CRRT (all that apply)
	Time from ICU admission to CRRT initiation
	Cumulative fluid balance from ICU initiation to CRRT initiation
Laboratory Data	Serum creatinine at ICU admission
	Serum creatinine at CRRT initiation
	APACHE II score at ICU admission

*CRRT* continuous renal replacement theray, *ICU* intensive care unit

%fluid overload = [(total fluid intake (L) – total fluid output (L))/ICU admission weight (kg)] x 100%. Additional patient clinical data will be updated on a daily basis to reflect clinical management, severity of illness and laboratory findings (Table 2). All laboratory values will be recorded as available, and no laboratory testing will be requested as part of CRRTnet.

**Table 2 Tab2:** Daily clinical data collection

Category	Data Elements
Severity of Illness	SOFA score components
	Need for mechanical ventilation
	Vasopressor requirements (drug and rate)
Fluid Balance	Type and volume of fluid intake
	Type and volume of recorded outputs
Nutrition	Enteral nutrition formula and volume
	Parenteral nutrition protein, calories and volume
Laboratory Data	Complete blood count: white blood cell count, hemoglobin, hematocrit, platelets
	Metabolic panel: sodium, potassium, chloride, bicarbonate, blood urea nitrogen, creatinine, phosphate, magnesium, albumin
	Coagulation parameters: INR, PTT, anti-Xa activity

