Data entry will be performed by trained study staff at each site, and will be entered into an online system using a password-protected web-based research interface (Watermark EDGE, Watermark Research Partners, Inc.). Electronic data transmission will utilize secure socket layer (SSL) encryption technology to maintain compliance with privacy and data security. Data within the Watermark EDGE database is protected by Transparent Data Encryption (TDE) encrypted with the AES-265 Cipher. Limited Data Set (LDS) will be collected with regards to specific dates for the following: year of birth, admission dates, treatment dates, date of discharge or death. For patient data entry each patient will be de-identified via assigned unique codes and will not contain direct traceable identifiers. This registry complies with the following as set forth in 45 CFR Parts 160 and 164 (“HIPAA Privacy Rule”): “Covered Entity” (45 CFR § 160.103), “De-identified information” (45 CFR § 164.514), “Protected Health Information (“PHI”)” (45 CFR § 164.103) and “Limited Data Set (“LDS”)” (45 CFR 164.514(e)(2)). All sites will utilize the same electronic report forms, with the exception of measurement units customized to match each center’s customary laboratory reporting. For purposes of analysis all unit values entered by the center will also be converted and stored in a standardized unit for reporting in addition to the original entry.

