### Operational definitions

Complete recovery: - Return of serum creatinine (SCr) to within 50% of baseline. Baseline SCr will be determined by the order of the following:
i.pre-hospital/outpatient SCr valuesii.lowest available in-hospital SCr (before or after) receiving CRRTiii.back calculation for a SCr based on an eGFR 75 mL/min using the CKD-EPI equation
2.Partial recovery: - No longer receiving RRT but SCr has not returned to within 50% of baseline.3.Non-recovery: - Remains dialysis dependent.

All serious adverse events related to CRRT will be recorded, with a specific focus on the following complications:Major bleeding event related to heparin anticoagulation:
i.Drop in hemoglobin of ≥1.0 g/dL within a 24 h period, *and*
ii.Transfusion requirement of ≥2 units packed red blood cells
2.Development of heparin-induced thrombocytopenia:
i.Fall in platelets of at least 30% *and*
ii.Positive confirmatory test for heparin-induced thrombocytopenia (serotonin release assay)
3.Hypocalcemia event related to citrate anticoagulation:
i.Fall in systemic ionized calcium below 0.8 mmol/L, *and one of the following*
ii.Worsening hypotension/increasing pressor requirement, *or*
iii.Cardiac arrhythmia

All serious adverse events will be reviewed with each site’s principal investigator to confirm appropriateness for inclusion.

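### Duration of AKI is tested by ANOVA or Kruskal-Wallis although it is not a listed outcome and has no observed end in patients who leave hospital on dialysis or die with AKI

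*Protocol article*

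**What the plan says.** The Statistical analysis section relates patient characteristics and CRRT parameters to "patient outcomes (mortality, length of stay, duration of AKI", using ANOVA for normally distributed variables and Kruskal-Wallis otherwise. It then announces multivariable proportional hazards models without naming their endpoint, time origin or censoring rule.

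The section Primary and secondary outcomes has a different kidney outcome. It states "The primary outcome will be patient survival at ICU discharge", then "Patient outcomes will also be recorded at hospital discharge", then "Additional outcomes include ICU and hospital length of stay, renal function recovery during hospitalization (defined above), and adverse events related to CRRT (defined above". Duration of AKI does not appear. Operational definitions makes recovery a status with three classes: complete (creatinine back to within 50% of baseline), partial ("No longer receiving RRT but SCr has not returned to within 50% of baseline") and non-recovery (still dependent on dialysis).

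For dates, Data collection lists "year of birth, admission dates, treatment dates, date of discharge or death". Table 1 has creatinine before CRRT at two moments, "Serum creatinine at ICU admission" and at CRRT initiation, and the time between ICU admission and CRRT initiation.

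**The concern.** The outcome list and the analysis paragraph name different kidney outcomes, and the one that is analysed does not suit the tests named for it. ANOVA and Kruskal-Wallis need one completed value per patient. Hospital discharge is the last stated assessment, and a patient who leaves on dialysis has no end of AKI by then; a patient who dies with AKI never has one. Two simple routes are open under these tests. One enters the time to discharge or death as if it were a finished duration. The other drops the patient, which takes out the worst kidney outcomes. Either can distort comparisons between CRRT practices, which are the purpose of the registry, and the first makes the result depend on how early each centre discharges its patients.

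**Working it through.** The document gives no figure for duration of AKI and no formal sample size calculation, so there is nothing to reproduce. Steps 1 to 4 compare the text. Steps 5 and 6 are illustrations on assumed distributions, in survivors only.

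**1. Outcome.**

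| Section | Kidney outcome |
|---|---|
| Primary and secondary outcomes | Recovery during hospitalization |
| Operational definitions | Complete, partial or non-recovery |
| Discussion (fluid removal) | Likelihood of renal recovery |
| Statistical analysis | Duration of AKI |

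Only the last row is a duration, and it has no counterpart in the outcome list.

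**2. Start.** No AKI onset date appears in Table 1, Table 2 or the list of dates. Two creatinine values, at ICU admission and at CRRT initiation, do not date onset.

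**3. End.** Complete recovery could mark an end. Non-recovery has none within the observation period. Partial recovery is open: the end could be the stop of RRT or a creatinine return that has not yet happened. Death with AKI cuts the duration short. The Background puts hospital mortality near or above 50% in ICU patients on RRT, so this group may be large.

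**4. Test.** Neither ANOVA nor Kruskal-Wallis can represent a censored value.

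**5. Illustration: a true difference shrinks.** Assume exponential time to recovery with median m = 14 or 28 days, and independent discharge at 3 days plus an exponential with median s. The recorded value is the earlier of the two times.

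- Share unrecovered at discharge = 2^(-3/m) × m/(m + s). For s = 14: 2^(-3/14) × 1/2 = 43% and 2^(-3/28) × 2/3 = 62%.
- The recorded median t solves t/m + (t - 3)/s = 1. For s = 14: 2t - 3 = 14 gives 8.5 days; 3t - 6 = 28 gives 11.3 days. Ratio 11.3/8.5 = 1.33, against a true 2.0.
- For s = 28: 29% and 46% unrecovered; medians 31/3 = 10.3 and 31/2 = 15.5 days; ratio 1.50.

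**6. Illustration: a false difference appears.** Two groups have the same true AKI duration (lognormal, log-SD 0.7, median 15, 25 or 40 days). Discharge is independent and lognormal (log-SD 0.6), with median 25 days in one group and 25, 22 or 20 in the other. Group size is 500 (2000 × 50% survivors = 1000, split in two) or 250. There were 1000 runs per setting, tested at 5%.

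| Gap in median discharge | Values set by discharge | Kruskal-Wallis rejects | Log-rank, censored at discharge, rejects |
|---|---|---|---|
| 0 days | 29–70% | 4–5% | 3–5% |
| 3 days | 31–72% | 13–77% | 4–6% |
| 5 days | 33–74% | 33–100% | 4–6% |

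The error comes from treating cut-off times as complete; it disappears when they are censored.

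**The case against.** The strongest case on the other side has five parts.

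- **No stated rule.** A reader might infer that the discharge date becomes the recorded value. The document does not say so: such patients could be excluded, censored, or ended when RRT stops. This stands, and it is why steps 5 and 6 are conditional. It does not rescue the named tests, since exclusion is selective and censoring is outside what they can do.
- **Proportional hazards models.** These handle censored times and may cover this outcome. That cannot be ruled out, but their endpoint is not stated. Variables also enter them on univariate significance below 0.2, so a distorted univariate test could carry through.
- **A condensed article.** Start, end and censoring rules for a non-primary variable may sit in a fuller protocol or SAP, and the outcome list need not be exhaustive. The absence of definitions is therefore not the finding. What remains is the disagreement between two stated sections and a stated test that does not fit.
- **Scoring may be possible.** Baseline creatinine may come from outpatient or other in-hospital values, and the source is the electronic record, so onset might be recoverable. Partly recovered patients are off RRT and treatment dates are collected, so their end might be too. Both are fair. To say that the variable cannot be scored at all, or that every partly recovered patient still has AKI, goes beyond the text.
- **Recovery is analysed elsewhere.** A reader might infer that the study's main hypothesis is left without its outcome. No main hypothesis is declared. The fluid-removal hypothesis in the Discussion names renal recovery itself, and further analyses by research question are provided for.

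**Conclusion.** The point holds in a limited form. The Statistical analysis section assigns ANOVA or Kruskal-Wallis to an outcome that is not in the outcome list, has no onset date among the listed items, and has no observed end in survivors discharged on dialysis, in patients who die with AKI, and possibly in those partly recovered. The stated tests can therefore mislead in either direction. A reader might infer a consistent pull towards no difference, but step 6 shows false differences as well.

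The size is unknown. The document gives no recovery rate and no distribution of recovery or discharge times, and the illustrations assume that discharge is independent of recovery, which is doubtful. They show that the effect could be material, not how large it will be. Primary survival is not affected. The change is worth making but is not critical.

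**What to change.** In Statistical analysis, replace duration of AKI with the outcome already defined: "renal function recovery during hospitalization (defined above", taken as recovery status at hospital discharge. Analyse it as a categorical outcome (complete, partial, non-recovery) with death as its own category. This costs only wording, because status and death are already planned.

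If a time measure is kept, run it from CRRT initiation to a defined recovery or RRT-stop date. Analyse it as cumulative incidence, with death as a competing event and patients discharged unrecovered censored at discharge, not by ANOVA or Kruskal-Wallis.

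The time measure has three costs. AKI length before CRRT is not estimated. The end date must be recorded: the article lists treatment dates, but does not say whether they cover dialysis after CRRT or how long daily creatinine continues. Censoring at discharge may be informative, because discharge is likely to depend on recovery, and this should be stated as a limitation.

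### The primary outcome is alive/dead status at ICU discharge, but the only adjusted model named is proportional hazards; an ordinary Cox model of death would not estimate the chance of surviving to discharge

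*Protocol article*

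**What the plan says.** Under Primary and secondary outcomes, the protocol article states: "The primary outcome will be patient survival at ICU discharge". This is a yes/no status, known for each patient when the ICU stay ends. The only later time point given is in the next sentence: "Patient outcomes will also be recorded at hospital discharge". The article mentions no vital status at a fixed day.

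Under Statistical analysis, associations are to be assessed with "patient outcomes (mortality, length of stay, duration of AKI") by the following tests: "using ANOVA (for normally distributed variables) or Kruskal-Wallis (for non-normally distributed variables"). These give unadjusted comparisons. The one multivariable method follows: "Multivariate proportional hazards models will be constructed". The section does not link that model to a particular outcome. It closes with "Additional analyses of registry data will be developed based on specific research questions". The article names no logistic, other risk-based or competing-risk model.

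**The concern.** The registry is meant to compare outcomes between CRRT practices without randomisation, so readers will rely on the adjusted results. The stated outcome is a status at discharge, while the stated adjusted model is one for rates over time.

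In an ordinary Cox model for death during the ICU stay, a patient who leaves alive can only be censored. Leaving alive is the favourable level of the primary outcome, so the censoring event is half of what the study wants to measure. The resulting cause-specific hazard ratio is a legitimate quantity, but it answers a different question. It compares daily death rates among patients still in the unit and ignores how quickly the others leave alive. Extending follow-up to hospital discharge moves the same problem to a later date.

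This matters when a practice also changes the rate of live discharge. The article lists length of stay among the outcomes to be related to CRRT practice, so it treats such an effect as possible. A practice that mainly prolongs ICU stay could then look protective on the hazard ratio. One that speeds recovery and discharge could look neutral or harmful.

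**Working it through.** The article gives no event count, power or effect size, so there is no figure of its own to reproduce. The check asks how far a Cox hazard ratio for death can depart from the primary-outcome contrast.

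**Inputs.**
- Target enrolment is 2000 (Sample size). An equal split of 1000 per group is assumed.
- Reference ICU mortality of 50% is assumed. The Background gives only hospital mortality for ICU patients on renal replacement, at about 50% or more, so 40% and 60% were also tried.
- All daily hazards are assumptions; none come from the article.

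**Formula.** Let d be the daily hazard of death in the ICU and l that of live discharge, both constant.
- ICU mortality = d/(d + l), so the odds of ICU death = d/l.
- Odds ratio = (d1/l1)/(d0/l0) = (d1/d0)/(l1/l0) = HR(death)/HR(live discharge).
- A Cox model that censors live discharges estimates d1/d0 = HR(death) only.

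The odds ratio and the hazard ratio therefore lie on opposite sides of 1 exactly when HR(death) lies strictly between 1 and HR(live discharge). In that case the practice moves both hazards in the same direction, and discharge more strongly.

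**Results.** Reference group: d = l = 0.05, mortality 50%.

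| HR(death), as Cox estimates | HR(live discharge) | ICU mortality in comparison group | Odds ratio | Reading |
|---|---|---|---|---|
| 1.20 | 1.80 | 0.06/(0.06 + 0.09) = 40.0% | 0.67 | opposite directions |
| 0.80 | 0.60 | 0.04/(0.04 + 0.03) = 57.1% | 1.33 | opposite directions |
| 1.00 | 0.70 | 0.05/(0.05 + 0.035) = 58.8% | 1.43 | HR null, mortality higher |
| 0.80 | 0.80 | 0.04/(0.04 + 0.04) = 50.0% | 1.00 | HR below 1, mortality equal |
| 0.80 | 1.00 | 0.04/(0.04 + 0.05) = 44.4% | 0.80 | same direction |
| 0.80 | 1.25 | 0.04/(0.04 + 0.0625) = 39.0% | 0.64 | same direction, different size |

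**Row 1 at the registry's size.** With 1000 per group, about 500 and 400 deaths are expected. SE(log HR) = √(1/500 + 1/400) = 0.067, and z = ln(1.20)/0.067 = 2.7. For mortality, z = 0.10/√(0.25/1000 + 0.24/1000) = 4.5. Both contrasts would usually reach significance, in opposite directions.

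**Row 2 by simulation** (150 data sets, 1000 against 1000).
- Mean ICU mortality was 49.9% against 57.0%.
- The Cox HR was 0.795, significantly below 1 in 93% of runs.
- The logistic odds ratio was 1.33, significantly above 1 in 87% of runs.
- Both were significant, in opposite directions, in 81% of runs.
- A Fine-Gray-type fit followed the risk direction (subdistribution HR 1.13).

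**Sensitivity of row 2 to the baseline.** Reference mortality of 40% gives 0.032/(0.032 + 0.036) = 47.1%. Reference mortality of 60% gives 0.048/(0.048 + 0.024) = 66.7%. The odds ratio is 1.33 in both.

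**The case against.** - **Link to the primary outcome.** The article never says that the hazards models are for the primary outcome. Length of stay and duration of AKI, for which such models are natural, stand in the same list as mortality. This is correct, and a reader should not infer that the plan commits the primary outcome to a censored Cox analysis. But mortality heads that list. If the hazards models are not meant for it, the article names no adjusted model for its primary outcome. Either way, the text needs clarifying.
- **Censoring is not forced.** A reader might infer that any proportional hazards model must censor live discharges. That is not so: a Fine-Gray model is also a proportional (subdistribution) hazards model and would fit the article's sentence. The criticism applies to an ordinary Cox model. The missing censoring rule is not the point either, since it may properly sit in a fuller document. The point is that the named model type does not match the named outcome.
- **Constructed examples.** The hazards are assumed, and reversal needs a specific condition. If a practice lowers death and leaves discharge unchanged or faster, the two measures agree in direction. This stands, and the documents do not support a claim that reversal is likely.
- **The date list.** A reader might take the date fields in Data collection ("admission dates, treatment dates, date of discharge or death") as a follow-up rule. They are an inventory of dates held, given in a privacy context, and carry no weight here.
- **Uses of hazards models.** The Discussion plans analyses of fluid removal rates, which vary over time. Hazards models suit these better than a plain model of status. This stands and is reflected in the fix.
- **Room for later analyses.** The closing sentence of the section leaves other models open, and status is recorded in any case, so no data are lost. This lowers the urgency, but analyses reserved for specific research questions do not supply a main model for the primary outcome.

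**Conclusion.** The point holds as a mismatch between two stated elements: a status outcome at ICU discharge, and proportional hazards as the only adjusted method, with no outcome attached to it. If that method is applied to death as an ordinary Cox model, its hazard ratio does not estimate an effect on ICU survival. Under constant hazards it departs from the primary-outcome odds ratio by the factor HR(live discharge). The direction reverses only when HR(death) lies between 1 and HR(live discharge). At the edges of that range, one measure is null while the other is not. Elsewhere they agree in direction but can differ in size.

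The algebra rests on constant hazards, and the sizes shown rest on assumed hazards and an assumed ICU mortality. The documents do not show that the registry's primary result will be wrong, nor that a cause-specific hazard ratio is invalid in itself. They do leave the adjusted analysis open to being read as an effect on ICU survival when it is not one.

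**What to change.** In Statistical analysis:

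- Name adjusted logistic or modified-Poisson regression as the main model for survival status at ICU discharge, and likewise at hospital discharge.
- State which outcomes the proportional hazards models serve, and keep them for time-to-event questions and time-varying exposures.
- For those models, treat live discharge as a competing event. Report the cause-specific hazards of death and of live discharge together, alongside cumulative incidence (for example, Fine-Gray).
- State that the death hazard ratio alone will not be read as an effect on ICU survival.

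Censoring live discharges remains correct when estimating the cause-specific hazard of death; what changes is how that result is presented and interpreted.

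The cost is a change of wording and slightly more analysis work, with no new data and no effect on recruitment. One real drawback is that time-varying exposures, such as daily fluid removal, need separate handling in the status model.
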